##### Family wellness plan

This dynamic document is created in a partnership between the mother and the NFN+ worker. NFN+ workers teach mothers SMART goal setting principles (specific, measurable, achievable, realistic, timely) and assist mothers in setting goals regarding their and their child’s health behaviors. A plan for self-monitoring behaviors, specific to the behavior (s) selected for the Family Wellness Plan, is determined. Self-monitoring calendars are used to document behaviors and are reviewed at each visit. Maternal success in achieving her goals is emphasized. The following specific behavioral targets are emphasized as goals: extending breastfeeding duration and exclusivity, no SSB/juice consumption until 6 months and then less than 6 oz/day for the next 6 months, no solids before 6 months of age and no cereal in bottles, improving parenting skills by establishing daily routines, reading infant cues related to sleep, hunger and satiety and infant physical activity (“Tummy Time”), no television viewing, and no television in the bedroom. As mothers are successful with these infant-directed targets, NFN+ workers begin to discuss ways to create a healthier food and activity environment for the mother utilizing nutrition programs (Cooking Matters^©^, visits to Farmer’s Markets/corner stores), activity programs (Yoga, Zumba) at the BFF Centers, and parenting classes. Mothers are encouraged to set small, personally meaningful and important goals and to document their goals and progress using self-monitoring calendars and a scrapbook (containing her Family Wellness Plan) created with her NFN+ worker.

##### Behavioral strategies

Modules for the core behavior skills are adapted from existing curricula (e.g. Husky Byte for SSB/juice [51, 52], Soothe/Sleep for routines [11]; Diabetes Prevention Program [53] for core behavioral skills relevant to healthy eating and activity) and include interactive activities. NFN+ workers teach mothers core behavioral skills (e.g., goal- setting) relevant to the specific behavior. Emphasis is placed on stimulus control and changing the home environment to support healthy choices (e.g., enhancing visual cues for good dietary choices).

All program materials are available in English and Spanish and have been developed and tested with home visitors, Latina and Black members of the community and parents for content, literacy and cultural relevancy. Concerns in Latina and Black mothers about weight as a sign of health [54], about being socially uncomfortable with breastfeeding [21, 55], childhood obesity as a non-issue [56], television as an educational tool [57], and outdoor safety as a barrier to exercise [58, 59] are addressed.

##### Intervention strategies

Activities within each intervention strategy module take ~10-15 min of the scheduled 60–90 min home visit and are delivered at different visits. Each targeted behavior is addressed in a series of interactive modules that can be divided into multiple 15-min segments. For example, the Sugar Sweetened Beverage Module has four “messages” linked to four activities. Message 1 stresses no juice in the first 6 months of life and comes with a bib that says “No Sugar drinks for me, I am sweet enough.” Message 2 teaches mothers to buy only 100 % fruit juice. Message 3 educates mothers about the sugar content of 100 % fruit juice and Message 4 stresses limiting juice consumption to less than 6 ounces a day from 6 months to 7 years of age. The messages build upon each other but can be delivered separately or together and in any order. NFN+ mothers are trained to recognize hunger and satiety cues in their infant and to establish sleep routines. Mothers are also taught how to use “Tummy Time” to enhance infant activity and development and how to avoid television viewing. In addition, mothers who are bottle feeding learn proper formula dilution, storage, and how to use hunger and satiety cues regardless of the milk volume consumed. The messages in each intervention module are described in Table 3.

**Table 3 Tab3:** Intervention modules and messages

Intervention module	Intervention messages	Intervention activities/Components
Feeding My Baby	1. Breast milk is best	-Picture of mom breastfeeding infant
	2. Breast milk is the only food a baby needs until 6 months	-3 reasons to breastfeed
		-Importance/Confidence rulers
	3. If formula feeding, mix formula correctly	-Goal setting tool
		-Steps to achieving goal
		-Barriers/Problem solving
		-Community resources to support activity: Heritage and Pride program
		-Self-monitoring calendar
		-Progress assessment
Juice/Sugar sweetened beverages	1. No juice or SSB before 6 months of age	-Picture of baby wearing “No sugar drinks for me” bib
	2. Serve only 100% juice	-Education around messages
	3. Sugar in 100% juice	-How to read a label to determine sugar content and addition
	4. No more than 4-6 oz juice/day	-Measuring cup, 6 oz sippy cup, bib,toothbrush
		-Importance/Confidence rulers
		-Goal setting tool
		-Steps to achieving goal
		-Barriers/Problem solving
		-Community resources to support activity: Cooking Matters, Shopping Matters
		-Self-monitoring calendar
		-Progress assessment
Little Tummy	1. Delay introduction of solids to 6 months	-Picture of baby (baby’s tummy)
	2. Do not add cereal to the bottle	-Education around messages
	3. How to introduce solids	-Measuring spoons
	4. What are the first solids	-Food card “quiz”
	5. Portion sizes	-Importance/Confidence rulers
		-Goal setting tool
		-Steps to achieving goal
		-Barriers/Problem solving
		-Community resources to support activity: WIC, Fruits and vegetable coupons
		-Self-monitoring calendar
		-Progress assessment
Screen Time	1. No TV/screen time under 2 years	-Picture of mother and infant looking at book, listening to music
	2. Remove TV from bedroom	-Education around message
		-Paper and crayons to make No TV sign
		-Importance/Confidence rulers
		-Goal setting tool
		-Steps to achieving goal
		-Barriers/Problem solving
		-Community resources to support activity: Brighter Future Family Center activities
		-Self-monitoring calendar
		-Progress assessment
Establishing Routines		
A. Rock-a-bye Baby	1. Infant sleep duration	-Picture of baby sleeping
	2. Create a healthy bedtime routine	-Education around messages
		-Sleep sack
		-Importance/Confidence rulers
		-Goal setting tool
		-Steps to achieving goal
		-Barriers/Problem solving
		-Community resources to support activity: Parenting support groups
		-Self-monitoring calendar
		-Progress assessment
B. Tummy Time	1. Use tummy time to play	-Picture of baby engaging in tummy time
		-Education around benefits of tummy time for baby and mother
		-Importance/Confidence rulers
		-Playmat
		-Goal setting tool
		-Steps to achieving goal
		-Barriers/Problem solving
		-Community resources to support activity: Parenting support group
		-Self-monitoring calendar
		-Progress assessment
C. Calm Baby	1. Techniques to soothe and calm baby instead of feeding	-Picture of mother holding baby
		-Education on hunger and satiety cues; strategies to calm baby
	2. Taking care of mother when infant is crying	-Importance/Confidence rulers
		-Goal setting tool
		-Steps to achieving goal
		-Barriers/Problem solving
		-Community resources to support activity: Parenting support group
		-Self-monitoring calendar
		-Progress assessment
Healthy Mom, Healthy Baby	1. Eat 5 servings of fruits and vegetables daily	-Picture of mother
		-Education about diet and physical activity; activity with her baby
	2. Get 10,000 steps a day	-Pedometer, Fruit and Vegetable coupons
	3. Be physically active 30 minutes/day 5 days/week	-Importance/Confidence rulers
		-Goal setting tool
		-Steps to achieving goal
		-Barriers/Problem solving
		-Community resources to support activity: Exercise classes, Cooking Matters, Shopping Matters
		-Self-monitoring calendar
		-Progress assessment

All modules have a similar format. Modules begin with introduction of a topic and the recommendation followed by education related to the rationale for the recommendation. The importance to the mother and her confidence to implement the recommendations are then explored using importance and confidence rulers. This is followed by the mother creating a goal for herself or her infant related to the module and problem-solving around the goal. A list of community linkages and a self-monitoring calendar are then provided by the NFN+ worker. The calendar and use of these community linkages are reviewed with the mother in later visits and the goals are reinforced. If a mother has been unsuccessful in achieving her goal, the goal is reviewed and revised with new problem-solving strategies and a new self-monitoring calendar is completed for subsequent review.

##### Toolkit

Mothers are provided with different items related to each module and a picture of their infant engaged in the activity is taken to encourage use. For example, for the juice modules, a measuring cup and 6 oz sippy cup are provided in addition to the bib described previously. For Tummy Time, a play mat is provided while no television is encouraged through creation of a sign that is placed on the television.

##### Linkages to relevant community programs

Each intervention module includes linkages to relevant community programs (e.g., Heritage and Pride for breastfeeding; BFF Centers for Yoga/Zumba and parenting classes, Cooking Matters^©^, Shopping Matters^©^, Husky Byte, FoodShare, Hartford Food System, and to WIC-approved and ECHO participating grocery/corner stores that accept program-created coupons for fruits and vegetables). When needed or appropriate, childcare and bus tokens are provided to facilitate use of these community programs. Intervention mothers are provided with fruit and vegetable coupons ($3/week) that they can use at local grocery stores and Farmers Markets. Mothers are provided with a pedometer to help track their steps each day. In addition, mothers can choose a “bonus” item such as cookware, a water filter system, bus passes, running shoes for themselves or a stroller. These bonus items were chosen because NFN workers noted that families were not able to participate in various activities such as cooking or exercise classes or walking activities because they didn’t have necessary items.

### Training

#### Training common to NFN and NFN+

All NFN and NFN+ Supervisors received training in the ethical conduct of human research and are certified. Additionally, they received two hours of training in how to obtain consent for the ECHO study and in how to complete each of the program’s questionnaires. Study staff accompanied the supervisors during the initial home visit to support the supervisors in obtaining consent and in completing the questionnaires.

#### Training unique to NFN+

NFN+ Supervisors and home visitors received 5 h of initial training and twice yearly formal booster sessions in ECHO including how to engage mothers in the behavioral change strategies and in how to render each of the intervention modules. They received an additional 4 h of training on the importance of breastfeeding, common breastfeeding problems, tips for successful breastfeeding and how to recognize abnormal breastfeeding by the Heritage and Pride program staff. A list of available resources to support mothers with breastfeeding and how to access these resources was provided. A study coordinator makes weekly visits to intervention centers to review the intervention module prior to delivery and to debrief with NFN staff after a home visit to assure consistency and completeness of the rendered intervention.

### Outcome measures

#### Demographics

Basic demographic information is obtained by self-report from mothers and is included in Table 1.

#### Process or intermediary variables

Message-specific maternal knowledge, intention and self-efficacy is being assessed using the Infant Feeding Practice Survey II [60, 61] adapted for prenatal and postnatal feeding practices and the Infant Feeding Style Questionnaire [62].

#### Primary outcome variables

Breastfeeding extent and duration and feeding behaviors related to solids and juices and sugar sweetened beverages are being assessed using questions from the Infant Feeding Practices Survey II and the Infant Feeding Style Questionnaire. Questions related to soothability have been extracted with permission from the Infant Behavior Questionnaire-Revised [63] and are administered at birth, 6 and 12 months. The Brief Infant Sleep Questionnaire [64] is being used to assess sleep patterns and duration. Questions about infant activity and television viewing are being used from other published studies [65, 66].

#### Secondary outcome variables

Maternal diet and behavior are being assessed using self- report on maternal fruits, vegetables, and beverage consumption [67]. Mothers are asked how many days per week they eat breakfast, lunch, dinner, and snacks and how many days per week they eat at fast-food or other restaurants. Information about the food and beverages in the home is obtained. The Paffenbarger Health Fitness Assessment is being used to assess maternal activity [68]. Infant weight and length with calculation of the weight for length *z*-score are determined by medical record review at birth, 6 and 12 months.

#### Additional variables

Three potential moderators of the treatment response are being assessed including the 4-item Perceived Stress Scale [69], the Family Social Support Questionnaire [70], and the Edinburgh Maternal Depression Screening Tool [71].

#### Additional measures in intervention arm

Doses of the intervention are being assessed using the home visitor logs and documented debriefings of home visits by home visitors with study staff, the number of returned fruits and vegetables coupons, documentation of activity in the Family Wellness Plan workbook and sign-in logs for activities at the Brighter Future Family Centers. Maternal satisfaction with the intervention and with specific modules in the intervention is being assessed using a satisfaction survey delivered by telephone by study staff at 6 and 12 months.

### Evaluation plan

Assessments will occur at birth and when the infant is 6 and 12 months. The Family Wellness Plan book is collected at 6 and 12 months and copied and returned to the family. Primary outcomes will be the child’s targeted behaviors at 12 months (i.e., extent and duration of breastfeeding, SSB consumption, timing of introduction of solids, sleep duration and soothability and television viewing) (Fig. 3). Assessed process variables include changes in mothers’ knowledge about dietary recommendations, intentions to make these changes, and self-efficacy to make healthy choices. Six month intermediary variables include changes in the home food environment and mothers’ shopping and cooking practices, child feeding styles, maternal stress, positive parenting practices, and community resource utilization. The RE-AIM analytic framework will be used [72, 73]. For RE-AIM, Reach will be explored by determining the percent of mothers/infants who were excluded and the reasons for exclusion, the percent of eligible mothers/infants who participated, and reasons for dropping out. Effectiveness will be evaluated by comparing differences in maternal behaviors at 6 months between control and intervention mothers and short-term attrition. For Adoption, intervention use (number of doses of each intervention and number of intervention types rendered) and NFN+ worker satisfaction and intention to use the intervention after study’s end will be evaluated. Implementation will be evaluated using the number of completed home visits and the association between these indicators and maternal behaviors. Maintenance will be assessed by examining child behaviors and weight for length *z*-scores at 12 months.

**Fig. 3 Fig3:**
[figure not shown]
Analytic plan for ECHO study

Threats to internal validity include family mobility, the population and neighborhood comparability, and their representativeness. To address these threats, we have limited eligibility criteria, paired the neighborhoods using important variables, and have sequentially enrolled eligible mothers to the target number per neighborhood. Hartford families return to the same Brighter Future Family Center and to the same clinic (e.g., <1 % change clinics each year [74]) and the NFN home visitor will provide continuity if the family moves but remains in the local area. Other threats include repeated testing and NFN+ worker bias. Where possible, we will use both objective (e.g., coupon use) and subjective (e.g., self-reported fruit and vegetable consumption) measures and will compare NFN and NFN+ home visit logs for content and visit frequency. Additional threats include NFN staff turnover. Threats to external validity include the patient population, attrition in the NFN program and the urban community.

#### Sample size, power calculation

This is an initial efficacy trial that is constrained by the size of the budget. However, 60 participants with a 20 % drop out rate is sufficient to detect a decrease of approximately 0.3 in the proportion of children under 6 months of age receiving SSB/juice and/or solid food with a power of 80 % and an alpha = 0.05.

### Statistical analysis plan for primary outcomes

The primary outcome measure is the duration and exclusivity of breastfeeding, the time to consumption of SSB/juice and solids, the amount of television/screen time per day, and sleep duration in NFN+ infants as compared to NFN infants. The quality of the randomization and the comparability of the participants have been assessed using >Chi square and t-tests as appropriate (Table 2). Participants were comparable except that intervention participants had higher parity as compared to control participants. Participants are nested and clustered within neighborhoods and these effects are being evaluated and will be controlled for in the statistical analysis. Using an intention to treat and a per protocol analysis, behaviors of NFN+ mothers will be compared to NFN mothers related to SSB/juice consumption (number of ounces per day, age at introduction of SSB/juice; age at beginning solids, duration (weeks) of breastfeeding and sleep duration, soothability, and television viewing hours) using two sample t-tests or Wilcoxon tests. Chi square analysis will be used to compare the proportions of exclusive breastfeeding at 6 months in the two groups. Similarly, we will determine if the intervention decreases the risk that infants would stop exclusive breastfeeding at any time considered in the study. A p ≤ 0.05 will be considered significant.

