**Fig. 2 Fig2:**
[figure not shown]
Study recruitment

**Table 2 Tab2:** Demographics of mother infant dyads

	Control (n = 23) (%)	Intervention (n = 26) (%)
Maternal age yrs (mean ± SD)	22.05 ± 5.73	24.35 ± 5.37
<18 years	2 (9 %)	1 (4 %)
18–30 years	18 (78 %)	21 (81 %)
>30 years	1 (4 %)	4 (15 %)
Parity (Primip) (%)*	21 (91 %)	6 (23 %)
Income	8 (35 %)	12 (46 %)
< $15,000	2 (9 %)	3 (12 %)
$15,000-$30,000	1 (4 %)	4 (15 %)
$30,000-$50,000	0 (0 %)	1 (4 %)
>$50,000	8 (35 %)	5 (19 %)
Do not know		
Race/Ethnicity	6 (25 %)	7 (27 %)
African American/Black	12 (52 %)	17 (65 %)
Hispanic	4 (17 %)	2 (8 %)
Other		
Marital Status: Married	3 (13 %)	7 (27 %)
Education	8 (35 %)	11 (42 %)
<12^th^ grade	6 (26 %)	5 (19 %)
High school or GED	7 (30 %)	7 (27 %)
>High school or GED		
Employment: Yes	8 (35 %)	10 (38 %)
Language spoken: English	21 (92 %)	18 (69 %)
Place of birth: United States	13 (58 %)	8 (31 %)
Public insurance	12 (52 %)	12 (46 %)
Maternal smoking (Yes, %)	5 (22 %)	6 (23 %)
Infant birth weight (Lbs) (Mean ± SD)	7.37 ± 0.83	7.36 ± 1.08
Infant sex (M, %)	12 (52)	9 (35)

Expressed as n (%) except as noted. Percentages may not add to 100 % due to rounding and missing data

*p < 0.001. All other differences were not significant

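### First-time mothers make up 21/23 of controls but 6/26 of the intervention arm, and no test named for the primary outcomes adjusts for parity, so a parity effect could mimic or mask an intervention effect

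*Protocol article*

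**What the plan says.** All references are to the protocol article.

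- **Table 2** gives primiparous mothers as 21 (91%) of 23 controls and 6 (23%) of 26 intervention mothers. Its footnote reads "p < 0.001. All other differences were not significant".
- **Statistical analysis plan for primary outcomes** draws this conclusion from the baseline comparison: "Participants were comparable except that intervention participants had higher parity as compared to control participants". It attaches no consequence for the analysis.
- The only adjustment in that section concerns clustering: "Participants are nested and clustered within neighborhoods and these effects are being evaluated and will be controlled for in the statistical analysis".
- Continuous outcomes are to be compared "using two sample t-tests or Wilcoxon tests". For the binary outcome, "Chi square analysis will be used to compare the proportions of exclusive breastfeeding at 6 months in the two groups".
- One further analysis has no named method: "we will determine if the intervention decreases the risk that infants would stop exclusive breastfeeding at any time considered in the study".
- **Additional variables** lists stress, social support and maternal depression as potential moderators. Parity is not among them. Nowhere in the article is parity a covariate, a stratification factor or the subject of a sensitivity analysis.
- **Overview and hypotheses** says that six centers were paired on neighborhood socioeconomic and racial/ethnic characteristics and that whole centers were randomized, three to each arm.

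**The concern.** Parity is known before the intervention starts. A mother's experience with an earlier child is plausibly related to breastfeeding, solids, juice, sleep routines and screen time, which are the primary outcomes. When parity differs between arms by 68 percentage points, a comparison that ignores it estimates the intervention effect plus a large share of the parity effect. The unadjusted result alone cannot show how much is which, or in which direction the parity part runs.

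The planned neighborhood control does not solve this. Each neighborhood lies wholly in one arm, so the arm effect is estimated between neighborhoods. Allowing for clustering mainly corrects the standard error and leaves the parity difference inside the contrast. The pairing did not use parity either.

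**Working it through.** **Inputs.** Table 2: 21 of 23 and 6 of 26 primiparous. Sample size section: target decrease of about 0.3 in the proportion receiving juice/SSB and/or solids before 6 months; 60 participants with 20% dropout, so 24 per arm. The effect of parity on the outcomes is not in the document. I assume 10 to 30 points for a binary outcome and 0.25 to 0.5 SD for a continuous one.

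**1. The stated imbalance reproduces.** 21/23 = 91.3%; 6/26 = 23.1%; difference 0.682. On the table [21, 2; 6, 20], chi-square = 22.96, p = 1.7 × 10⁻⁶ (continuity-corrected 6.7 × 10⁻⁶; Fisher 1.7 × 10⁻⁶). This agrees with p < 0.001.

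**2. Share of a parity effect that enters the arm difference.** If parity shifts the outcome by g and the intervention does nothing, the expected arm difference is (21/23 − 6/26) × g = 0.682g. The error rates below are for the uncorrected chi-square test at two-sided 0.05, by exact enumeration, with outcome rates centered at 50% and clustering ignored.

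| Assumed parity effect | Spurious arm difference | False-positive rate |
|---|---|---|
| 10 points | 6.8 points | 7.5% |
| 20 points | 13.6 points | 15.4% |
| 30 points | 20.5 points | 29.3% |

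For a continuous outcome, parity effects of 0.25 and 0.5 SD give t-test error rates of about 9% and 21% (simulation, 20,000 runs).

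**3. Cost of adjusting, if the two other controls are multiparous.** The arm-parity correlation is (21×20 − 2×6)/√(23×26×27×22) = 408/596.0 = 0.685. Variance inflation is 1/(1 − 0.685²) = 1.88, and the standard error rises by √1.88 = 1.37, or 37%. The effective sample is 49/1.88 = 26 dyads. With 24 per arm and a 0.3 decrease from a control rate of 50% or 65% (the article's background figures for juice/SSB and solids), approximate two-sided power falls from 0.59 or 0.55 to 0.35 or 0.32, before clustering.

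**4. Cost if those two controls have missing parity.** Table 2 warns of missing data. In the control arm, age categories sum to 2 + 18 + 1 = 21 and education to 8 + 6 + 7 = 21, the same number as are recorded primiparous. If parity is missing for two controls, the table is [21, 0; 6, 20]. The imbalance factor is 1 − 0.231 = 0.769. The correlation is (21×20 − 0×6)/√(21×26×27×20) = 420/543.0 = 0.77, and variance inflation is 1/(1 − 0.7735²) = 2.49. There would then be no multiparous controls.

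**5. Restricting to first-time mothers (21 vs 6).** With equal outcome variance, the variance ratio to the full comparison is (1/21 + 1/6)/(1/23 + 1/26) = 0.2143/0.0819 = 2.6, so the standard error is about 62% larger.

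**The case against.** **The article is condensed.** It flags the imbalance openly and never says that parity will be ignored. Covariate lists are often left to an analysis plan, and the analytic-plan figure is not shown. The promise to control for neighborhood also implies something beyond a bare t-test. What stands: the named tests are not the whole analysis, and one breastfeeding analysis names no method, so it would be wrong to say that every planned analysis is unadjusted. But the article reports the imbalance after enrollment and, in the same paragraph, names tests that take no covariates. The one adjustment it does promise cannot separate parity from arm.

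**Adjustment is fragile.** With 49 dyads in six centers and at most two multiparous controls, an adjusted estimate leans on the model. A primary model that also carries pair terms and a random center effect is open to debate. This stands, and it is why the conclusion must be limited whichever analysis is used.

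**Stronger readings that the document does not support:**

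- *That a false benefit would be reported.* The direction and size of any parity effect are not given, so a real effect could equally be hidden.
- *That centers enrolled differently.* Table 2 has no center-level counts.
- *That this is the trial's largest source of bias.* Nothing in the document allows a ranking. It is the largest documented baseline imbalance.
- *That the arms also differ in language and birthplace.* English-speaking (21/23 vs 18/26) and US-born (13/23 vs 8/26) give Fisher p = 0.080 and 0.088. Neither contradicts the table's footnote.
- *That exactly two controls are multiparous.* They may have missing data. The table does not settle it, since control race/ethnicity sums to 6 + 12 + 4 = 22.

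**Conclusion.** The point holds. The plan acknowledges a 68-point parity imbalance, names only tests that leave it unadjusted, and relies on a neighborhood adjustment that cannot remove it. Followed as written, the primary comparisons carry about 68% of any parity effect (77% if two controls have missing parity).

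The proportion rests on Table 2 alone. Its translation into 7, 14 or 20 points rests on assumed parity effects of 10, 20 or 30 points. If parity had no bearing on an outcome, the bias for that outcome would be zero. Even at a 20-point parity effect, the spurious difference is nearly half the 30-point target. Adjustment cannot fully rescue the comparison, because the arms overlap too little on parity to separate the two effects precisely.

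**What to change.** 1. For each primary outcome, including the analysis of stopping exclusive breastfeeding, pre-specify an arm comparison adjusted for parity (primiparous yes/no) that keeps the planned neighborhood control. Report it beside the unadjusted result.
2. State that no intervention effect will be claimed from the unadjusted result alone, and that arm and parity overlap too little to be separated precisely.
3. Confirm from the data whether the two non-primiparous controls are multiparous or have missing parity, and give the parity denominators in Table 2. If parity is missing, say that any adjusted estimate for multiparous mothers is extrapolation, and treat the comparison within first-time mothers (21 vs 6) as the only one supported by overlap.

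No new data collection is needed. Parity is already recorded and precedes the intervention, so adjusting for it introduces no post-treatment bias. The cost is precision: variance inflation of about 1.9 (standard error up 37%) if the two controls are multiparous, and about 2.5 if their parity is missing, in both cases before clustering.

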Understanding the context in which obesogenic behaviors occur, helping parents of very young children to establish positive behaviors, and linking families to community resources could prevent the development of obesity in young children. These goals are the foundation of an intervention called the *Early Childhood Obesity Prevention Program (ECHO): Building Healthier Families and Communities.* ECHO is a randomized, controlled trial designed to examine the efficacy at 12 months of a home visitation program that engages mothers as agents of change to modify their own behavior and their infant’s behavior through education and skill building in the areas of nutrition, physical activity, and wellness, and then “echoes” her training with linkages to neighborhood programs (e.g., coupons to purchase fruits and vegetables at grocery stores and farmer’s markets, parenting classes at Family Centers, neighborhood cooking classes). ECHO recruits pregnant women and new mothers who have agreed to participate in NFN’s home visitation program and provides them with an enhanced curriculum that increases maternal skills in goal-setting, problem-solving, and stimulus control to target four specific infant-related behaviors (breastfeeding, SSB/juice consumption, introduction of solids, television/screen time and infant routines and cues around sleep and hunger and satiety) and follows the mother-infant dyad until the infant is 12 months of age. The program also provides education and linkages to community resources to improve the mother’s health, nutrition and physical activity. The study’s focus on newborns and mothers as agents of change adds to the small literature on obesity prevention in this critical developmental window.

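### Breastfeeding duration and ages at first juice and solids are censored times, yet the plan gives them t-tests or Wilcoxon tests; the harm lies mainly in breastfeeding duration and in early dropouts

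*Protocol article*

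**What the plan says.** The statistical analysis plan for primary outcomes includes "the time to consumption of SSB/juice and solids" in its definition of the primary outcome, beside breastfeeding duration and exclusivity. It then lists "age at introduction of SSB/juice; age at beginning solids, duration (weeks) of breastfeeding" with sleep, soothability, television hours and daily ounces, all to be compared "using two sample t-tests or Wilcoxon tests", by intention to treat and per protocol.

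The only risk-over-time wording is for another variable: "we will determine if the intervention decreases the risk that infants would stop exclusive breastfeeding at any time considered in the study". It names no method and does not extend to the three times above.

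The Background says that the study "follows the mother-infant dyad until the infant is 12 months of age". The Evaluation plan states: "Assessments will occur at birth and when the infant is 6 and 12 months". The sample size section allows for loss: "60 participants with a 20 % drop out rate is sufficient to detect a decrease of approximately 0.3". The article gives no value or rule for a dyad that reaches 12 months, or leaves, without the event.

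**The concern.** A mother still breastfeeding at 12 months has no observed duration, and an infant who has had no juice by then has no age at introduction. The Family wellness plan section sets an upper limit on juice after 6 months, so an infant can reach 12 months with none. A dyad lost before the event is also censored, on any of the three outcomes.

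A t-test or Wilcoxon test needs a number for each dyad, which leaves three options:

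- **Drop event-free dyads.** For breastfeeding and juice these are the best results, and an effective intervention makes them more common. Dropping them pulls the comparison toward no effect and fits poorly with intention to treat.
- **Enter the last known age for dropouts.** This records an event nobody saw. If one arm loses more dyads, that arm appears to stop breastfeeding, or start juice or solids, sooner.
- **Enter 52 weeks.** This works for dyads followed to 12 months, but has no basis for those lost earlier.

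These are primary outcomes, so the choice should not wait until the data have been seen.

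**Working it through.** **Inputs from the article.** 60 dyads with 20% dropout: 60 × 0.8 = 48, or 24 per arm. Follow-up is 12 months (52 weeks) and the significance level 0.05, taken as two-sided. Background rates at 6 months are 50% for juice or sugar-sweetened beverages and 65% for solids. The article gives no figure for these analyses to reproduce; its power statement concerns a proportion under 6 months and is not used here.

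**Assumptions.** No 12-month event rates are given, so those below are assumed. Dropout times in the simulations are uniform. Clustering is ignored.

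**Step 1: effect of dropping event-free dyads (closed form).** Take exponential times, control median 26 weeks, hazard ratio 0.5, no dropout.

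- Hazards: ln 2 / 26 = 0.0267 per week (control) and 0.0133 (intervention).
- Event-free at 52 weeks, S = exp(−52 × hazard): 25% and 50%, so 6 and 12 of 24 dyads would be dropped.
- 52-week restricted mean, (1 − S)/hazard: 28.1 and 37.5 weeks; difference 9.4.
- Mean among events only, 1/hazard − 52S/(1 − S): 37.5 − 17.3 = 20.2 and 75.0 − 52.0 = 23.0 weeks; difference 2.8.

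Dropping therefore hides 1 − 2.8/9.4, about 70%, of the 12-month difference.

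**Step 2: simulated power, exponential times, hazard ratio 0.5, 24 per arm (1,500 or 2,000 trials where the number of runs is recorded).** Last age means the event age if observed, otherwise age at last contact or 52 weeks.

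| Controls event-free at 52 weeks | Dropout | Log-rank | t, last age | Wilcoxon, last age | t, events only |
|---|---|---|---|---|---|
| 25% (median 26 weeks) | 0 | 47% | 39–41% | 41–44% | 7–8% |
| 25% | 20% | 45% | 33–34% | 33–34% | 7% |
| 10% | 20% | 54% | 45% | 41% | 14% |
| 20% | 20% | 47% | 37% | 37% | 9% |
| 30% | 20% | 41% | 31% | 30% | 7% |
| 5% (median 12 weeks) | 0 | 61% | 57% | 52% | 24% |

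The collapse from dropping dyads grows with the event-free share.

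**Step 3: type I error, no true effect.** With equal dropout every method stays near 5%. With 10% versus 50%, last-age coding gives about 10% to 13%, against 5% to 6% for log-rank; the arm losing more dyads looks 3.7 weeks shorter on average (20% event-free). With 10% versus 30% it gives about 6%, little different from log-rank.

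**Step 4: an early effect with catch-up, as could occur for solids and juice.** Control rates at 6 months are those in the Background, reduced by the 0.3 of the sample size section; 12-month rates are assumed; no dropout.

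| Outcome, control/intervention at 6 then 12 months | t, capped at 52 | Wilcoxon, capped | Log-rank | t, events only |
|---|---|---|---|---|
| Solids 65/35, then 98/98 | 44% | 44% | 29% | 48% |
| Solids 65/35, then 97/95 | 47% | 47% | 35% | 48% |
| Juice 50/20, then 80/70 | 45% | 41% | 28% | 43% |
| Juice 50/20, then 85/85 | 34% | 30% | 14% | – |

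Without dropout, the t-test on values capped at 52 weeks is a comparison of 52-week restricted means. Under this pattern that comparison keeps its power and log-rank does not.

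**The case against.** The strongest reply is that the article never says event-free dyads will be dropped. It promises intention to treat, which points the other way, and their coding could sit in the full plan. With full follow-up and 52 weeks entered for event-free dyads, Wilcoxon remains valid and loses little (41% to 44% against 47%), and a capped t-test estimates a restricted mean. All of this stands. A reader might infer that the planned analysis will have under 10% power; the documents do not support that, because the figure belongs to one coding that they neither adopt nor exclude.

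A reader might also carry the loss over to all three outcomes. That does not stand either. The Little Tummy module in Table 3 delays solids to 6 months and then teaches their introduction, so few infants should be event-free at 12 months. Step 4 shows that even an events-only t-test need not collapse there.

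Nor is a log-rank or Cox replacement free of cost: it loses power when the effect is confined to the first 6 months. A Cox model with a random centre effect on six centres, adjusted for parity (91% versus 23% primiparous), may be unstable with about 48 dyads.

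What the reply does not answer is dropout. The article names the tests, so this is a stated method and not only a missing detail. With the 20% loss it expects, neither test has a sound value for a dyad lost before its event.

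**Conclusion.** The point holds in limited form: the stated tests do not suit right-censored times. It bears mainly on breastfeeding duration, and on early dropouts for all three outcomes.

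For breastfeeding duration at hazard ratio 0.5, treating dropouts as events costs roughly 10 percentage points of power (about 34% against 45% at a control median of 26 weeks). Dropping event-free dyads leaves under 10% if 20% or more of controls are event-free at 12 months, and more if fewer are (14% at 10%, 24% at 5%). Type I error is at risk only when dropout is strongly unequal. With complete follow-up and 52 weeks entered, the loss is small.

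The sizes rest on assumed event rates, exponential times (except step 4), uniform dropout and no clustering. The mismatch between outcome and test does not depend on them. Exclusive breastfeeding has its own risk wording and lies outside this point.

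**What to change.** For breastfeeding duration, age at first juice or sugar-sweetened beverage, and age at first solids:

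- Replace the t-test/Wilcoxon with Kaplan-Meier curves and a comparison of 12-month restricted mean time.
- Censor at 12 months or last contact, and state the assumption that dropout is unrelated to the outcome.
- Keep the planned control for neighborhood.
- Offer a log-rank, Cox, discrete-time or interval-censored analysis as supportive. The last two suit assessments held only at birth, 6 and 12 months.

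Keep t-tests or Wilcoxon tests for sleep, screen time, soothability and ounces per day.

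The cost is a change of wording before analysis and slightly more analysis work, with no new outcome to collect; a last-contact date per dyad is needed. The restricted mean should lead because log-rank or Cox would lose power if the effect on solids or juice is confined to the first 6 months.
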